### **Analysis of primary outcomes.**

The data will derive from a randomized controlled trial (RCT) with random assignment of individual participants to one of two study conditions (intervention vs. control). Data will be collected at baseline and posttest. The primary outcomes include measures of diet, weight, physical activity, stress, depression, alcohol use and tobacco use. Each of these measures will be self-reports using established scales that have evidence of reliability (internal consistency and/or test-retest reliability) and validity, as described below..

Primary analysis. The primary analysis will be an analysis of covariance (ANCOVA) wherein the intervention and control conditions are compared at posttest with regression adjustment for baseline values on the dependent variable. We will also consider using the measure of Health and Job Control as a covariate, along with potential confounders, as mentioned below. The test of the intervention effect will be the t-test for the regression coefficient for condition, which will estimate the adjusted difference between the two conditions at posttest. That test will be two-tailed with a type I error rate of 5%. We will perform the analysis using SAS PROC GLM, Version 8.2 (SAS Institute, 2001).

Assumptions. ANCOVA is based on the General Linear Model (Searle, 1971). It assumes that the dependent variable is a linear function of the predictors, that the errors are independent, and that the errors have a normal distribution. These assumptions are commonly met in most RCTs involving continuous dependent variables, especially when treatments are delivered to individuals, as will be the case here. Even so, we will examine the residuals from the models to confirm that they are normal. Our experience with these variables indicates that the assumption of normality will be met. If it is not, we will assume a more appropriate distribution or consider a transformation to normalize the data.

Missing Data. The primary analysis will employ intention-to-treat principles. Because randomization carries the expectation of creating treatment groups equivalent with respect to known and unknown prognostic factors, removing randomized participants from the analysis runs the risk of tampering with this balance and introducing bias into the treatment comparisons. As a result, all participants randomized into the study will be included in all analyses irrespective of protocol violations and events arising post randomization and all participants will be analyzed according to the treatment to which they were randomized. We will make a concerted effort to track, locate and measure all participants at the follow-up surveys. However, even with our best efforts, we can anticipate that there will be some missing data; based on our previous work, we estimate that we will lose no more than 20% of the sample. Multiple imputation is now widely regarded as an effective method for replacing missing data. In particular, we will fit a logistic regression equation using baseline data from participants in the control condition to predict participation status at follow-up. We will use that equation to generate a predicted value to replace each missing value in both conditions,

adding a value for residual error generated from a distribution matching the follow-up participation status distribution in the comparison condition. By repeating that procedure several times, we will obtain several complete data sets that differ only in the values imputed to replace the missing data. We will then analyze those data sets and combine their results to provide a summary estimate and test for the intervention effect. We will employ SAS PROC MI and SAS PROC MIANALYZE, Version 8.2, to implement these multiple imputation procedures (SAS Institute, 2001).

Confounding. Though randomization of 150 participants to each condition makes it unlikely that there will be any imbalance of prognostic factors between the two conditions, confounding remains a possibility in any single realization of an experiment. Left alone, such imbalance could confound the true relationship between condition and the outcomes. In order to avoid this problem, we will examine prognostic factors measured at baseline for evidence of any imbalance; if it is present, we will perform secondary analyses in which we repeat the primary analysis adding the potential confounders as additional covariates in the ANCOVA, attending carefully to issues of measurement error, which can create problems for such adjustments. Regression adjustment cannot completely correct for confounding, but to the extent that the confounders are well measured and properly modeled, the adjusted analysis will reduce the bias created by those confounders.

Effect modification. Other secondary analyses will explore the assumption of homogeneity of the intervention effect across subgroups of participants. Though power will be limited for interactions, we will add a subgroup main effect and a condition x subgroup interaction to the ANCOVA in order to explore possible interactions. The primary subgroup variables will be gender, age group, and racial or ethnic group.

Alternative analytic strategies. Several alternative analytic strategies were considered. The data could be analyzed using a repeated measures analysis of variance model, wherein condition, time (baseline and the two posttests) and their interaction are included as independent variables. However, this approach tends to have less power than the analysis proposed here, and it also makes unnecessary assumptions about the structural relationship between the baseline and posttest values of the outcome variables. For those reasons, we prefer the ANCOVA.

(D) a list of investigational devices that will be used, indicate if they are classified as significant risk (SR) or non-significant risk (NSR) devices and whether there is an IDE or there is an application to the FDA for an IDE if the device is SR;

N/A

(E) a statement that defines who will be financially responsible for the costs associated with participation in the study (e.g. examinations, procedures, drugs, devices, etc.) and a statement that defines what will be provided without cost to the subjects;

ISA will be responsible for all costs associated with participation in the study. Participants will be asked to complete the survey and program review (for experimental group participants and managers) on their own time and not during work time.

(F) your assessment of whether the research involves any physical, psychological, social and/or economic risk(s) and the magnitude of the risk(s);

The potential risks of collecting the data are quite minimal. It is possible that participants could become uncomfortable when responding to the survey questions. To minimize this risk, participants will complete their questionnaires in private and their names will not be associated with their data. In addition, the survey questions will be phrased in ways to minimize any

potential discomfort. While the risks of the field survey are minimal, it is possible that a participant may, as a function of participating in the field test, recognize one or more serious medical problems requiring immediate attention. The program will include a number of resources that the participant can use and steps to take in the event of an acute or serious problem. Users will be referred to the resources section at several junctions of the program and a list of resources both nationally and locally, will be provided to those requiring further assistance. A disclaimer will be listed at the beginning of the program that says the site is designed to educate users and provide them with the skills to effectively reduce their risk for disease, but that they should seek the advice of a medical care provider if additional assistance is needed. Additionally, the consent form will point out this potential risk and inform participants that they should call their health care provider if they need immediate assistance.

(G) your assessment of the risk/benefit ratio of the research;

The potential risks of the research to participants seem minimal, and are far outweighed by the anticipated benefit. These benefits include the development of an effective, interactive web-based program that can educate older workers on health risks and wellness and prevent health and financial problems associated lifestyle factors. All participants will benefit by receiving access to the *HealthyPast50* program (either as part of the program evaluation or, for control group participants, after the surveys are completed). We believe that the minimal risk associated with participation is quite reasonable when compared to the benefit that participants and the larger society can receive from reducing or preventing the development of acute or chronic disease among older workers.

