### 2. State purpose of study:

The overall goal of this project is to develop and test a comprehensive, interactive, and innovative web-based program designed to improve the health of older workers. This program will address a wide variety of health behavior topics, including physical activity, nutrition/weight management, stress management, mood management, alcohol use, and tobacco use – the health behaviors that contribute to the likelihood of contracting major diseases. The program will be tested with working adults 50 years of age and older.

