## **Outcome Measures**

A draft copy of the survey questionnaire is attached. Most of the measures will be self-report scales of health behaviors that the ISA research team has used in several research projects during the past decade (e.g., Cook et al., 1996a, 1996b, 2004, 2005, 2007; Deitz et al., 2005; Billings et al., 2008)) and will therefore have the typically desired psychometric underpinnings -- established reliability coefficients, validity estimates, etc. -- as described below. In addition, several of the scales were developed and validated by other investigators -- e.g., Block et al., 1986; Schwarzer and Renner, 2000; Glynn and Ruderman, 1986 -- but have demonstrated evidence of reliability and validity. For all scales, however, psychometric analyses will be conducted on the measures once the data are in order to ensure that the collection of items can be legitimately summated; e.g., whether they have high Alpha coefficients and high item-total score correlations. The questionnaire will include the following measures:

☐ **Demographics** -- Items assessing respondents' age, ethnicity, marital status, education, and income. These items have been associated with differences in health outcomes and will be

used as control variables in our multivariate models. They may also be used in interaction terms, or as moderators when applicable.

- ❑ **Symptoms of Distress** – A 15-item scale developed by Orioli et al. (1991) and used in multiple studies by our team (Cook, et al., 2003; Billings et al., 2008). Four items assessing the behavioral signs of stress (e.g., overeating, criticizing others) were summed with four other items assessing the physical signs of stress (e.g., muscle tension, headache). A recent randomized trial (Billings et al., 2008) generated an Alpha of .069. Evidence of validity was generated from Cook et al. (2003) and Billings et al. (2008) where the measure showed significant decreases in subjects exposed to stress management interventions.

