- ❑ **Coping With Stress** – A 12-items scale assessing the type of strategies one uses to cope with difficult situations and events. Two subscales are imbedded in the survey – adaptability and situation mastery. Adaptability measures flexibility in coping strategies and situation mastery measures the ability to recognize when and how to appropriately react to stressors. Questions are answered on a 4 point likert scale ranging from never to almost always. Typical questions include: “I often put things aside for a while to get perspective on them”; or “I decide certain problems are not worth worrying about”. (Alpha for the scale was .76 in a previous ISA study).
- ❑ **Nutritional Patterns** – This 12-item scale assesses the nutritional value of the respondent’s diet. It is a modification of the Block Self-Administered Diet History Questionnaire, developed and validated by Block and her associates (Block et al., 1986). The original Block questionnaire was found to correlate 0.70 with more detailed food recall methods, and a later validation study (Block et al., 1990) found that the questionnaire produced group mean nutrient estimates closely approximating the values obtained by three 4-day records. The Nutritional Patterns scale was used by our group in the test of the workplace “Healthy Eating” program with 210 employees of the GMAC insurance company (Cook et al., 2003), in which program participants showed significant improvements in their Nutritional Patterns scores from pretest to posttest ( $F = 77.37$ ,  $p < .001$ ) with an Alpha of 0.64.

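### Depression is declared a primary outcome, but the protocol's own list of questionnaire measures contains no depression or mood scale

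*Protocol*

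**What the plan says.** Under Analysis of primary outcomes (Narrative, part C), the protocol states: "The primary outcomes include measures of diet, weight, physical activity, stress, depression, alcohol use and tobacco use". The next sentence but one in substance promises an instrument for every one of them: "Each of these measures will be self-reports using established scales that have evidence of reliability", together with evidence of validity, and it says that the descriptions follow.

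The instruments are described earlier, under Outcome Measures (part B). That section opens with "A draft copy of the survey questionnaire is attached" and introduces its list with "The questionnaire will include the following measures". The list runs from Demographics to Belief About Aging.

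Item 2, on the purpose of the study, describes the program's content as "including physical activity, nutrition/weight management, stress management, mood management, alcohol use, and tobacco use". Mood is therefore something the intervention sets out to change.

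The primary analysis is an ANCOVA that compares the two conditions at posttest, adjusted for the baseline value of the same outcome.

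**The concern.** The two sections do not fit together. One makes depression a primary outcome and says its scale is described; the other describes the questionnaire's measures and includes no such scale.

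The choice of instrument is a data-collection decision, so a statistical analysis plan could not repair this later. The declared ANCOVA needs a depression score at both pretest and posttest. Under part A of the Narrative, the pretest is completed before randomization and controls receive the program once the posttest is done. A pretest score that was not collected cannot be obtained afterwards, and there is no later randomized comparison to fall back on. A scale added only at posttest would allow an unadjusted comparison, but not the declared primary analysis.

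Two outcomes are then foreseeable: a declared primary outcome goes unreported, or another scale is given its name once the data are in. Both are selective-reporting problems.

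**Working it through.** No formula applies, and the protocol gives no figure on this point to reproduce. The check sets the seven primary domains beside the 16 bullets under Outcome Measures.

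| Primary domain | Listed measure |
|---|---|
| Diet | Nutritional Patterns, Eating Practices and other eating scales |
| Weight | Height and Weight |
| Physical activity | Exercise Habits |
| Stress | Symptoms of Distress; Coping With Stress |
| Depression | none |
| Alcohol use | Alcohol use quantity/frequency |
| Tobacco use | Tobacco Use |

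The remaining bullets are demographics, attitude and self-efficacy scales for diet and exercise, two planning measures, and beliefs about aging. None concerns depression or mood. Result: 6 of 7 domains have a listed measure and 1 of 7 does not.

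**Is the scale described elsewhere?** The analysis section says the descriptions follow it, but no scale is described from that point to the end of the protocol. The word depression occurs only in the list of primary outcomes. Mood occurs only as a program topic in item 2.

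**Could a listed scale serve as the depression measure?** There are two near candidates.

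- Symptoms of Distress is described as follows: "Four items assessing the behavioral signs of stress (e.g., overeating, criticizing others) were summed with four other items assessing the physical signs of stress". This is stress content, and stress is already a primary outcome in its own right.
- Coping With Stress is described as follows: "Two subscales are imbedded in the survey – adaptability and situation mastery". This is about coping strategies, not mood.

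The protocol nowhere assigns either scale to depression.

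**Consequence if the list is followed as written.** No depression score exists at pretest or posttest, so the ANCOVA has neither a dependent variable nor a baseline covariate for that outcome.

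**The case against.** A reader might infer that the questionnaire itself has no depression measure and that the data are already certain to be lost. The documents do not support that, for three reasons.

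- The draft questionnaire is an attachment that is not in the text available. What can be shown is a gap in the protocol's list, not in the survey.
- The list may be incomplete. The analysis section also mentions a Health and Job Control measure as a possible covariate, and that is not listed either.
- Symptoms of Distress is called a 15-item scale, but only 4 + 4 = 8 items are described. The content of the other 15 − 8 = 7 is not stated, so mood content in them cannot be ruled out.

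The word depression may also be a drafting remnant. The analysis section says the scales are described below when they are described above. The paragraph on alternative analytic strategies refers to two posttests, although the study procedures have one. Part E mentions managers as program reviewers, although they appear nowhere else as participants. If depression is a leftover, no intended data are lost and the correction is editorial.

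These points limit how far the conclusion can go, but they do not remove the contradiction. The list is presented as the questionnaire's content and is not marked as partial. If the attachment does hold a depression scale, the protocol still fails to name it or give its scoring and its evidence of reliability and validity, although it says each primary outcome's scale is described. If the word is a remnant, the primary outcome list is wrong. The seven undescribed distress items do not make that scale a depression measure, since the protocol presents it only as a stress scale.

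**Conclusion.** The point holds as an internal contradiction: a declared primary outcome has no instrument in the protocol's own list of measures. Confidence in that mismatch is high, because it can be read directly from the text.

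Its size is one of seven primary domains, and it also touches one of the six program topics named in item 2. The analyses of diet, weight, physical activity, stress, alcohol use and tobacco use are not affected by it.

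The consequence is conditional. If the attached questionnaire contains no depression scale, the declared analysis for depression cannot be done, and the gap becomes permanent once the pretest is collected. If it does contain one, what remains is an incomplete description of a primary outcome measure. The documents do not show which of these applies.

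**What to change.** Before the pretest opens, check the attached questionnaire for a depression or mood scale. Then do one of the following:

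1. **Keep the outcome.** Name a validated self-report depression scale under Outcome Measures, with its items, scoring and evidence of reliability and validity, and include it in both the pretest and the posttest surveys. If the scale is already in the questionnaire, this costs a paragraph of text. If it is not, it also costs a few more items at each of two administrations.
2. **Drop the outcome.** Remove depression from the primary outcomes and state that the mood management component is not evaluated. This costs one deleted word and one added sentence.

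In either case, do not designate Symptoms of Distress as the depression outcome after the fact. In the same edit, reconcile the Health and Job Control covariate with the measures list, since it has the same kind of gap.

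### The multiple-imputation rule models participation status, not the missing posttest outcome, and applies that control-only equation to both arms of the primary analysis

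*Protocol*

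**What the plan says.** The rule is in the Protocol, item 16, part (C), Missing Data paragraph under Analysis of primary outcomes. It has three linked steps:

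1. The model: "we will fit a logistic regression equation using baseline data from participants in the control condition to predict participation status at follow-up".
2. Its use: "We will use that equation to generate a predicted value to replace each missing value in both conditions".
3. The added noise: "adding a value for residual error generated from a distribution matching the follow-up participation status distribution in the comparison condition".

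The steps are repeated to give several completed data sets, and then: "We will then analyze those data sets and combine their results to provide a summary estimate and test for the intervention effect". The same paragraph commits to intention to treat, in that "all participants randomized into the study will be included in all analyses irrespective of protocol violations and events arising post randomization", so the imputed values enter the primary test. On the amount of missing data it says: "we estimate that we will lose no more than 20% of the sample".

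The outcomes concerned are set out at the start of the same section: "The primary outcomes include measures of diet, weight, physical activity, stress, depression, alcohol use and tobacco use". The primary analysis is an ANCOVA in which "the intervention and control conditions are compared at posttest with regression adjustment for baseline values on the dependent variable".

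**The concern.** What is missing is a posttest score, a weight or a count. What is modelled is whether a person took part in follow-up. The prediction from such a model is a probability of participation, and the stated residual distribution is also that of participation. Participation status is named twice, once as the modelled variable and once as the source of the residual, so this is hard to set aside as a single slipped word. A participation model can support weighting, but here it is told to supply the values themselves. Nothing else in the protocol gives an imputation model for the outcome.

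A second feature matters even if the outcome was intended. The equation is fitted in control participants only and applied to both arms, so each missing intervention value is drawn as though that person had been a control. That is a strong assumption about dropouts, and the protocol neither states nor defends it.

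The rule governs the primary estimate and test for every primary outcome. It is a rule the protocol fixes, not a detail it leaves open.

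**Working it through.** The protocol gives no effect size, SD or power, so there is no planned figure to reproduce.

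**Inputs from the protocol:** 150 per arm; two-sided 5% test; ANCOVA; estimated loss of 20%, that is 300 × 0.20 = 60 people, or 30 per arm if equal, leaving 120 completers per arm.

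**Assumed, not in the protocol:** true effect 0.3 SD; baseline-posttest correlation ρ = 0.6; example scales with mean 30 and SD 6, or mean 2 and SD 3; data missing at random, with equal loss unless stated. Each result below was also simulated (ANCOVA, 10 imputations, Rubin's rules).

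**A. Reference: outcome imputed within arm**
- SE = √(1 − 0.6²) × √(2/120) = 0.8 × 0.129 = 0.103 SD.
- Power = Φ(0.30/0.103 − 1.96) ≈ 83%. The simulated mean estimate is 0.30 SD.

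**B. Literal rule: gaps filled from the participation model**

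With 20% loss the fill-in values average about 0.8. The mean estimate is (1 − 0.20) × 0.30 = 0.24 SD.

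Residual variance of the filled outcome, for mean μ and SD σ:

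V = 0.8 × 0.2 × (μ − 0.8)² + 0.8σ² + 0.2 × 0.16 − (0.8 × 0.6 × σ)²

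- Mean 30, SD 6: V = 136.4 + 28.8 + 0.03 − 8.3 = 157.0. SE = √157.0 × √(2/150) / 6 = 0.241 SD. Power ≈ Φ(0.24/0.241 − 1.96) ≈ 17%; simulated 15% to 17%.
- Mean 2, SD 3: V = 0.23 + 7.2 + 0.03 − 2.07 = 5.39. SE = √5.39 × √(2/150) / 3 = 0.089 SD. Power ≈ Φ(0.24/0.089 − 1.96) ≈ 77%; simulated 72% to 75%.

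The loss is therefore severe when the scale's mean is far from 0 to 1 in SD units, and small when it is not.

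**C. Literal rule with unequal loss and no true effect**

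Spurious difference = (difference in loss) × (μ − 0.8) / σ. At 25% loss in control and 15% in intervention:
- Mean 30, SD 6: 0.10 × 29.2 / 6 = 0.49 SD. Against SE 0.241, rejection ≈ Φ(0.49/0.241 − 1.96) ≈ 52%; simulated about 50% to 55%.
- Mean 2, SD 3: 0.10 × 1.2 / 3 = 0.04 SD. Against SE 0.089, rejection is about 7%.

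At 22% versus 18% on the first scale, the simulated rejection rate is 13%. The sign depends on which arm loses more.

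**D. Charitable rule: control-only model for the outcome, used in both arms**

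Let I and C be the adjusted completer means. The filled intervention mean is 0.8 I + 0.2 C and the filled control mean is C, so the estimate is 0.8 × (I − C).
- Dropouts keep the effect: 0.8 × 0.30 = 0.24 SD, which is 20% too small. At 10% intervention-arm loss the shrinkage is 10%. The factor does not depend on correlation or scale.
- True sampling SE: 0.8 × 0.103 = 0.083 SD (about 0.085 with imputation noise). Simulated Rubin's-rules SE: about 0.105.
- Type I error: 2 × [1 − Φ(1.96 × 0.105/0.085)] ≈ 1.5%; simulated about 1% to 2%.
- Power: 1 − Φ((1.96 × 0.105 − 0.24)/0.085) ≈ 66%; simulated 65%, against 83% in A.
- Dropouts gain nothing: the true effect in all randomized is 0.8 × 0.30 = 0.24 SD. The control-only rule gives 0.24. Within-arm imputation gives 0.30, which is 0.30/0.24 = 1.25 times the truth.

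**Sensitivity.** At ρ = 0.5 with a true 0.3 SD, simulated power is 76% (within arm), 60% (control-only) and 16% (literal, mean 30, SD 6). With a true 0.4 SD it is 93%, 85% and 25%.

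**The case against.** **Likely a drafting slip.** The paragraph names SAS PROC MI. A programmer would probably impute the outcome, and a 0 or 1 entered as a body weight would be noticed at once. That is fair as a forecast. But the analyst would then be departing from the written rule and choosing an unwritten one, for the primary analysis of every outcome.

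**Control-based imputation is legitimate.** It is a recognised conservative option. In a voluntary web program, dropout may well go with non-use, and if dropouts gain nothing it is the within-arm method that overstates the effect (part D). This stands, and it rules out a reading that a reader might adopt: that the control-only equation always biases toward zero. It does so only if dropouts keep the benefit. What remains is that the protocol does not offer this rationale and still predicts the wrong variable.

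**The power figures depend on the reviewer's inputs.** True. The literal rule is nearly harmless on some scales, and the alcohol and tobacco measures include counts and yes/no items of that kind. Any single power figure would mislead, hence the range.

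**Two other inferences should be resisted.** A reader might conclude that the regression coefficients are held fixed across imputations. The text says only that the procedure is repeated, which can include refitting, so that is not a finding. A reader might also take 20% as a ceiling on missing data; it is the protocol's own estimate of loss.

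**Conclusion.** The rule is wrong as written and must be corrected before analysis. The wrong target variable and the control-only fit are both explicit, and no other part of the protocol repairs them.

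The consequence depends on the reading:
- **Literal:** power anywhere from about 15% to 75% instead of 83%, and false positives when loss differs by arm (about 55% in the 25% versus 15% example on a mean-30, SD-6 scale, far fewer on a low-mean scale).
- **Charitable:** about 20% shrinkage at 20% intervention-arm loss, if data are missing at random and dropouts keep the effect. The standard error is too large, so the cost is power and not false positives. If dropouts gain nothing, this version is unbiased.

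The need to correct rests on the literal wording. The charitable reading alone would call only for a stated rationale. The effect size, correlation, scale values and arm-specific losses are all assumptions.

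**What to change.** Rewrite the imputation steps of the Missing Data paragraph:

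- Delete the participation-status model as the source of imputed values.
- Impute each missing posttest outcome itself, with a model suited to its scale: linear regression or predictive mean matching for scores, logistic regression for binary items.
- Include treatment arm in the model, or fit it by arm, together with the outcome's baseline value and baseline predictors of dropout.
- Combine results with PROC MIANALYZE, as already planned.
- Keep control-based imputation of the outcome as a labelled sensitivity analysis for the case where dropouts gain no benefit.

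The cost is one reworded paragraph and a few lines of code. No new data are needed and the sample size is unaffected.
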